#### Sham-acupressure group

In this group, five non-acupoints are used as controls. A non-acupoint is defined as a point on the body not falling on the acupoints depicted in the two TCM reference books [38, 39] and agreed by the members of the expert panel. The five non-acupoints are the root of the nasal bone (point 1), the olecranon of the ulna (point 2), the ulnar styloid process (point 3), the medial malleolus (point 4), and the head of the fibula (point 5). Pressure is applied on the five non-acupoints in the same way as in the AG. Point 1 is first pressed for 3 minutes. Points 2 and 3 are next pressed simultaneously for another 3 minutes. Finally, points 4 and 5 are pressed simultaneously for the last 3 minutes. For the bilateral points (that is, points 2, 3, 4, and 5), the points on one side are pressed in each session and they are pressed alternatively along sessions. The intervention dose and duration are the same as in the AG. The participants in this group receive a free course of acupressure sessions, identical to the one stipulated in the AG, after completing the study.

#### Usual-care group

In this group, participants receive no acupressure-related intervention. They receive a free course of acupressure sessions, identical to the one stipulated in the AG, after completing the study.

### Outcome measurement

The primary outcome in this study is the change of agitation (that is, CMAI score), and the secondary outcome is the change in stress ( measured by salivary cortisol concentration). The outcomes will be measured at the baseline (T0), the week immediately after completion of the intervention (T1), 2 weeks after completion of the intervention (T2), and 6 weeks after completion of the intervention (T3). The measurement at T1 aims to examine the immediate effect after the intervention, that at T2 aims to examine the peak effect, and that at T3 aims to examine the delayed effect. The decision to use the measurement interval of T2 and T3 was based on the result of the pilot study [32], where weekly repeated measurement showed that the effect of acupressure peaked at the time point 2 weeks after the completion of intervention and diminished to very close to baseline at the time point 6 weeks after the completion of intervention.

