**Discussion:**

This trial will provide a higher quality of evidence than previous studies on the use of acupressure for agitation in PWD. It will also provide newer evidence on acupressure in the population of PWD with agitation for clinical application and further research, including the effect on moderating stress, the delayed effect, the added effect on the placebo, and the effect on moderating the participant’s use of psychotropic drugs.

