Preliminary studies [26–28] have shown that acupressure can reduce agitation in PWD. However, given that the participants and the RCH staff providing the outcome observation were not blinded in the previous studies, the extent of the placebo effect could not be estimated. Previous studies showed that manipulative therapies, such as massage [23, 29] and therapeutic touch [25, 30], had also reduced the agitation and stress of PWD. These studies led the present researchers to hypothesize that acupressure may produce an agitation-reducing effect by mediating the stress hormone (that is, cortisol) through tactile stimulation alone, instead of via acupoint stimulation. Many other factors that might account for the effect were not reported in previous studies, such as the delayed effect of the intervention and the use of psychotropic drugs.

Therefore, we designed the present study primarily to investigate the effectiveness of acupressure for reducing agitation, compared with sham-acupressure and usual care. Meanwhile, we further investigated the effect of acupressure on stress moderation (that is, reduction of cortisol level), the delayed effect, the efficacy of acupressure in addition to the placebo effect (that is, compared with the sham-acupressure), and whether acupressure leads to a reduction in psychotropic drug use.

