**Participants/next-of-kin**					
Informed consent	x				
Sign the proxy consent	x				
Obtain participant’s assent	x				
Access medical record	x				
Physical examination	x				

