**Outcomes**					
Agitation (CMAI)		x	x	x	x
Stress (salivary cortisol)		x	x	x	x

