## Discussion

The results of this study will primarily answer the question whether acupressure demonstrates a significant effect in a tightly controlled trial (with maximum possible blinding and stringent control of the intervention implementation fidelity). One of the key active components of acupressure, differentiating it from other manipulative therapies (for example, massage, therapeutic touch), is the activation of acupoints. This study first provides a sham-acupressure group to compare the efficacy difference of acupressure between tactile stimulation and acupoint stimulation. This study uses a relatively shorter intervention duration. A shorter duration of therapy may favor greater compliance with the intervention in the clinical application. This study is the first to use a bio-marker (that is, salivary cortisol) and the extent of the use of psychotropic drugs to track the outcome of the intervention. These may provide a more objective comparison of effects. Finally, this study is also the first to examine the delayed effect of the intervention. This may also provide a reference for clinical application.

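### Psychotropic drug use is a stated secondary aim, but the outcome list and the assessment schedule include no measure of it and no collection after baseline

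*Protocol article*

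**What the plan says.** Three places in the protocol article present psychotropic drug use as something the trial studies:

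- The Background lists among the further questions "whether acupressure leads to a reduction in psychotropic drug use".
- The Discussion part of the Abstract promises evidence on "the effect on moderating the participant’s use of psychotropic drugs".
- The main Discussion presents as novel the use of salivary cortisol together with "the extent of the use of psychotropic drugs to track the outcome of the intervention", and calls these potentially more objective comparisons.

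Two places define what is measured and when:

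- Outcome measurement states: "The primary outcome in this study is the change of agitation (that is, CMAI score), and the secondary outcome is the change in stress", the latter measured by salivary cortisol. It ties T0, T1, T2 and T3 to those outcomes.
- Table 1 has two rows under Outcomes, CMAI and cortisol, each marked at Weeks 0, 3, 5 and 8. Its Monitoring block covers compliance, reasons for withdrawal and adverse events. The row "Access medical record" has one mark, at Week -2.

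The Blinding section includes the physicians who prescribe psychotropic drugs and the nurses who give them among those to be blinded. It concedes that blinding is not possible for the usual-care group.

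**The concern.** An aim stated three times has no counterpart in the part of the plan that says what will be measured. Three things follow.

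First, a team that carries out the listed outcomes and the schedule exactly will finish without the data this aim needs.

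Second, if the data are gathered anyway, nothing in the article fixes the measure. Drug use can be expressed by drug class, by dose, by as-needed administrations or as any change in prescription, over various windows. A definition chosen once results are visible carries little evidential weight.

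Third, drug use helps to explain the primary result. The Background itself faults earlier studies for not reporting factors that might account for the effect, and names psychotropic drugs as one of them. Usual care is unblinded, and the ethics section says its participants are told to wait for their compensatory treatment. Drug changes could therefore differ by arm, and without drug data the report could not say whether they did.

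**Working it through.** The point rests on comparing sections and counting scheduled assessments. The sample size of 99 (33 per group) plays no part in it and is not affected.

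**1. What the aim requires.** A change in drug use within a participant needs one assessment at baseline and at least one later. Even a comparison of post-treatment use between groups, without a baseline, needs at least one assessment after baseline.

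**2. What is scheduled.** From Table 1:

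| Item | Columns marked | Marks after baseline (Weeks 3, 5, 8) |
|---|---|---|
| CMAI | Weeks 0, 3, 5, 8 | 3 of 3 |
| Salivary cortisol | Weeks 0, 3, 5, 8 | 3 of 3 |
| Psychotropic drug use | no row | 0 of 3 |
| Medical record access | Week -2 | 0 of 3 |

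The schedule has none of the post-baseline assessments that step 1 requires.

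**3. Whether the text fills the gap.** Outcome measurement uses the singular for both levels: one primary outcome, and "the secondary outcome is the change in stress". It does not present these as examples. The Analysis section names no drug-use variable. No section gives a measure, a source or a collection time for drug use.

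**4. Whether this is only condensation.** The main Discussion pairs cortisol and drug use as the two objective ways of following the intervention. Cortisol appears in the outcome list and at four time points in Table 1; drug use appears in neither. The table is detailed enough to give separate rows to assent and physical examination. The article's aims and its outcome list therefore disagree with each other, which is more than detail left to a fuller document.

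**5. Room for later choice.** As an illustration only, with definitions that are not in the article: four ways of expressing drug use (class, dose, as-needed use, any change) at three post-baseline times give 4 × 3 = 12 candidate analyses, before any choice of look-back window or of which groups to compare.

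**The case against.** The strongest reply is that the article signals an intention to collect these data. The Discussion describes drug use as a measure, and prescribers and drug-administering nurses are to be blinded. A full protocol may contain the definition, and nursing-home medication records can be read retrospectively. Much of this stands, and it rules out several stronger readings:

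- **That the trial cannot answer the question.** A reader might infer this from the schedule. The article supports only the narrower statement that the outcome list and schedule, followed as written, do not answer it. The data may in practice be collected.
- **That the single record-access mark shows drug data to be unobtainable.** The row sits with consent, assent and physical examination, and documented dementia is an inclusion criterion. It may be only an eligibility step, and it does not say that records are closed afterwards.
- **That prescribers and nurses are blinded in order to serve the drug-use aim.** The Blinding section gives no reason. Preventing unequal co-treatment would explain it equally well.
- **That the CMAI difference cannot be interpreted without drug data.** The randomised intention-to-treat comparison still estimates the effect of allocation, including any prescribing changes that follow from it. The article reports no differential prescribing.

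The reply does not remove the disagreement between the stated aim and the closed outcome list. An intention that can only be inferred also does not fix a definition in advance.

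**Conclusion.** The inconsistency is real and limited to a secondary aim. Psychotropic drug use is announced in three places, is absent from a closed list of two outcomes, and is scheduled at 0 of 3 post-baseline time points. As written, the plan leaves this aim unanswered, leaves any later analysis open to post hoc definition, and leaves differential drug changes undescribed. The primary outcome, the sample size and the validity of the randomised CMAI comparison are untouched.

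This rests on two readings: that Outcome measurement is meant as a complete list, which its wording and its match with Table 1 support, and that Table 1 shows the full assessment schedule. If a fuller protocol already defines and schedules the measure, only the published text needs to be aligned with it.

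**What to change.** Reconcile the sections now. The article says the trial is still recruiting, so the definition can be settled before results are known. There are two acceptable routes.

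1. **Keep the aim.** Add psychotropic drug use to the secondary outcomes in Outcome measurement and add a row to Table 1. State one measure, its source (the homes' existing medication records) and its collection at baseline and at T1, T2 and T3. How long a look-back window to use is a matter of choice, provided it is fixed beforehand and is the same in all arms. Compare the groups in the intention-to-treat population and report the result alongside CMAI. Do not adjust the primary CMAI analysis for drug use after randomisation, because treatment may itself affect it.
2. **Drop the aim.** Remove it from the Background and the Abstract, and remove the claim in the main Discussion that drug use tracks the outcome.

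The first route costs a small amendment and modest record extraction at three further time points, with no new procedure for participants. The second costs only edits to the text, but it gives up a question the authors present as a novelty of the trial.

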### Training and quality control

All research personnel, those conducting the intervention, and data collectors must attend an 8-hour training course consisting of one lecture and two skills workshops provided by two of the six members of the TCM expert panel. This training is intended to ensure that they comply with the research protocol. All personnel conducting the intervention have to pass a skill examination administered by one of the six members of the TCM expert panel. The test contents included correct identification of the acupoints (for example, skills on identifying landmarks and the Deqi sensation) and acupressure techniques (for example, skills on sustaining the pressure by fingers). The test was performed on both the elderly volunteers and the trainer (that is, one of the six members of the TCM expert panel). The interventionist could only pass the test when the skills were observed by the trainer to be up to standard and the pressure felt by both the elderly volunteer and the trainer to be optimal (that is, experience the Deqi sensation sustainably for 3 minutes) as depicted in the protocol. To prevent fatigue, one interventionist was assigned to conduct acupressure for less than 10 sessions in a whole day and adequate rest time between sessions was provided. All data collectors and research assistants have to pass the skill examination stipulated by the researchers before they can become involved in this study. The training content for the personnel conducting the intervention strictly followed the intervention protocol of the study, with complete agreement by the expert panel. The training content for data collection made reference to the original instruction manual of the related instruments [34, 41].

In order to control the quality of the intervention and data collection, all the data collectors and those conducting the intervention have to attend a separate skill evaluation provided to the research team monthly. There are also on-site visits once to each site to monitor the skill of the data collectors and those conducting the intervention. Dropout, withdrawal, undelivered intervention and uncollected data are recorded until completion of the study.

### Safety and adverse events

All adverse events (for example, unfavorable or unexpected signs and symptoms after the treatment) are monitored. Regular meetings are held among the research team and the RCH staff in order to review the trial protocol and participant safety, and to explore possible adverse events. Participants who experience suspected adverse events are excluded from the study after discussion among the research team, RCH staff and the family. If there is clear evidence of any threat to the safety of the participant, the trial will be terminated.

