### Statistical methods

#### Sample size estimation

To estimate the sample size using G*Power® [43], with assumptions (that is, α =0.05, power =0.8, three groups), estimated effect size (that is, f =0.27) and attrition rate (that is, 10%) from the pilot study [32] and the previous similar studies [26, 27], the total number of samples needed in a randomized controlled trial to demonstrate a significant mean difference among the three groups is 99. There will therefore be 33 participants in each group.

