#### Analysis

Data analysis will be performed by a statistician blinded to the whole trial process using IBM SPSS Statistics 20 software [44]. The level of significance will be reported at *P* <0.05. Both per-protocol and intention-to-treat analysis will be used in order to provide more information on the effect of the intervention, considering possible confounders such as non-compliance, protocol deviations and withdrawal [45]. The per-protocol population is defined as participants who completed the study without major protocol violation (for example, who received more than 80% of the acupressure sessions). The intention-to-treat population is defined as participants who are randomized into groups after the collection of baseline data. Demographic and clinical data will be analyzed at baseline to measure the balance among the three groups. The results will be described by mean and standard deviation for continuous data, and by frequency and percentage for categorical data. The general estimated equation model will be used to compare the effects among groups and time points.

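### The adverse-event rule removes randomised participants from the study, so outcomes are lost for people the intention-to-treat population is meant to include

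*Protocol article*

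**What the plan says.** Under Safety and adverse events, the protocol article first says that "All adverse events (for example, unfavorable or unexpected signs and symptoms after the treatment) are monitored". It then sets the rule for a participant who has one: "Participants who experience suspected adverse events are excluded from the study after discussion among the research team, RCH staff and the family". The removal is from the study, not only from the intervention. No section says that CMAI or salivary cortisol is still collected afterwards.

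Under Analysis, "The intention-to-treat population is defined as participants who are randomized into groups after the collection of baseline data". A separate population covers completers: "The per-protocol population is defined as participants who completed the study without major protocol violation".

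Under Outcome measurement, the primary outcome is the change in CMAI score, measured at baseline (T0) and at three visits after the intervention (T1, T2, T3). Table 1 schedules adverse-event monitoring and the recording of reasons for withdrawal through week 8. Training and quality control adds that dropout and uncollected data are logged.

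**The concern.** The intention-to-treat definition depends only on randomisation. The safety rule then takes some of those people out because of something that happens after randomisation and may be caused by the allocated treatment. They stay in the population on paper, but their later outcomes are not measured. In practice the intention-to-treat analysis moves towards the completer analysis that the plan already has under the name per-protocol.

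This cannot be left to an analysis plan. It is a data-collection rule, and no later model recovers values that were never taken.

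Two things are at stake. The comparison with usual care may be distorted if removals are unequal by arm and related to outcome. Safety follow-up also ends early for the participants in whom an event was suspected.

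**Working it through.** **1. The two rules side by side.** Take a participant randomised after baseline who has a suspected adverse event in the first treatment week. By the Analysis section this person belongs to the intention-to-treat population. By the Safety section this person can leave the study. Treatment lasts two weeks and T1 comes after it, so only T0 would exist. No change in CMAI, the primary outcome, can be formed. The log of uncollected data records that loss but does not repair it.

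**2. Is the loss likely to be equal across arms?** In the acupressure arm, pressure is raised until soreness, numbness, distention or heaviness is felt or inferred from behaviour. The sham arm is pressed in the same way, with the same dose and duration. Usual care receives no pressure. The article's own example of an adverse event is a sign or symptom following treatment. More events in the two pressure arms than in usual care is therefore plausible, though not documented.

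**3. Is the removal independent of allocation and outcome?** It follows a discussion that includes the research team, and the Acupressure group section has researchers applying the pressure. It also includes nursing-home staff, and the Blinding section has formal caregivers among those staff supplying the CMAI data and concedes that usual care cannot be blinded. Nothing separates the decision from allocation or outcome.

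**4. Size.** The article states no event or exclusion rate, so there is no figure of the plan to reproduce here. Assumed inputs:
- share of an arm removed, p: 0.05 to 0.10, which of 33 people is 33 × 0.05 = 1.65 to 33 × 0.10 = 3.3
- CMAI change in those removed, worse than in those retained by D: 0.5 to 1.0 SD

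The full arm mean is (1 − p) × retained mean + p × removed mean. The retained mean therefore differs from the full mean by p × D:
- low: 0.05 × 0.5 = 0.025 SD
- high: 0.10 × 1.0 = 0.10 SD

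**5. Yardstick.** The Sample size estimation section gives f = 0.27 for three groups. The largest difference between two arms depends on the pattern of means:
- one arm differs from two equal arms: d = f × 3/√2 = 0.27 × 2.121 = 0.573
- evenly spaced means: d = f × √6 = 0.27 × 2.449 = 0.661

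| Shift | Relative to 0.573 | Relative to 0.661 |
|---|---|---|
| 0.025 SD | 4% | 4% |
| 0.10 SD | 17% | 15% |

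These percentages treat the SD of the change and the SD behind f as the same. With equal variances this is exact when the two visits correlate 0.5, since 2 × (1 − 0.5) = 1.

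**6. By comparison.** If nobody is removed from usual care, a pressure arm's contrast with usual care shifts by the full 0.025-0.10 SD. If both pressure arms lose people within the assumed range, the acupressure-sham contrast shifts by the difference of two such amounts. That lies between 0.025 − 0.10 = −0.075 and 0.10 − 0.025 = +0.075 SD, and is zero when the losses are alike.

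**7. Cross-check.** Suppose instead that removal follows a normal liability correlated r with outcome. The shift is then r × φ(z)/(1 − p), with z the upper-p normal quantile. For r from 0.3 to 0.8, p = 0.05 gives 0.033-0.087 SD and p = 0.10 gives 0.058-0.156 SD. With r = 0 there is no shift.

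**The case against.** The strongest reply is that nothing is contradicted. An excluded participant still meets the intention-to-treat definition, so data are lost but membership is not. The plan expects withdrawals, runs both analyses, monitors adverse events through week 8 and logs missing data. The signs and symptoms following treatment are an example, not a definition, and removal is not automatic.

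Part of this stands. No text removes these people from the analysis set, and unequal removal by arm is an inference. But keeping someone in a population without measuring the outcome gives little of what intention-to-treat is for, and the article nowhere says that scheduled monitoring continues for a person who has been excluded.

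A reader might infer more than the documents support:
- **That the planned GEE is unweighted and cannot correct the loss.** The article says only that "The general estimated equation model will be used to compare the effects among groups and time points". Weighting, working correlation and missing-data handling may sit in a plan not shown. In a simulation with no true effect (15% removed from one arm, removal correlated 0.5 with outcome, visits correlated 0.5), GEE with an exchangeable correlation was within 0.006 SD of no bias when removal depended on observed baseline or T1. When removal depended on unobserved outcomes, the bias was 0.06-0.07 SD with exchangeable and 0.10-0.12 SD with independence correlation. A model assuming missing at random would not cure that second case, so no change of model is asked for.
- **That people vanish from the treated arms only, in favour of acupressure.** Monitoring is not restricted by arm. A favourable shift also requires that those removed would have done worse, and it concerns mainly the comparison with usual care. Sham participants are pressed in the same way, so against sham the losses may cancel or go either way.
- **That these losses add to the planned 10% attrition.** That allowance may already include them.

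**Conclusion.** The concern holds as a conflict between two stated rules. Read literally, the safety rule ends outcome collection for some randomised participants, while the analysis is meant to cover everyone randomised.

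The possible bias is modest: 0.025-0.10 SD in an arm mean, or about 4-17% of an effect of d = 0.57 to 0.66. This rests on an assumed 5-10% removal and an assumed 0.5-1.0 SD worse outcome, neither of which the article gives. If removal is unrelated to outcome, it causes no bias. Where it is related, recruiting more people does not reduce the bias. The comparisons with usual care are the ones mainly exposed, and no direction is established against sham. The early end of safety follow-up does not depend on these assumptions.

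**What to change.** Reconcile Safety and adverse events with Analysis by one added statement: a suspected adverse event does not by itself end study participation; T1 to T3 outcomes and safety follow-up continue where consent and assent allow; and the participant is analysed in the allocated group. Any decision about treatment is left as it stands, and this point takes no view on it.

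The cost is a short amendment and a few more staff-reported CMAI assessments and saliva samples. At the assumed rates this concerns about two to three people in an arm of 33. The article describes the trial as still recruiting, so data not yet lost can still be collected.
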